### Outcome measures

#### Primary

The primary outcome measure will be falls, defined as “an unexpected event in which the participants comes to rest on the ground, floor or lower level” [59]. Falls will be monitored during the 6 weeks intervention and for 12 months thereafter, consistent with the recommendations of the ProFaNE consensus group . Participants will mark all falls on the day they occur on a falls calendar, [60]or mark a month without falls by ticking a box marked “I had no falls”. Pre-paid envelopes will be provided for the return of each month’s calendar sheet. Injurious falls, defined as a fall requiring medical attention or any healthcare utilization, will be marked with a yellow sticker. Telephone calls will be used to remind participants who have not returned their monthly sheet. Calls will also investigate each injurious fall using a set questionnaire that examines the health and economic sequelae of the fall based on data from Medicare Australia, self-reported health care utilization and out-of-pocket expenditure.

#### Secondary

Secondary outcome measures include changes in motor disability, global disability and quality of life. Changes in motor disability and global disability will be compared from pre- to post-therapy (T1 to T2) and from T2 to 12 months after therapy ceases (T3), using respectively the motor section III of the MDS-UPDRS [53,61] and the full MDS-UPDRS. The MDS-UPDRS is the current version of the original UPDRS [62], augmented and revised in line with the findings of its review taskforce (MDS, 2003), and represents the gold standard in PD assessment. Quality of life will be evaluated on the same occasions, using the disease-specific PDQ-39 [54,55] which has demonstrated validity, reliability and sensitivity. The widely used generic EQ-5D [58] will allow comparison of quality of life with non-PD populations [63].

### Economic evaluation

To enable calculation of the costs of the intervention relative to the number of falls prevented, the direct costs of implementing the therapy programs including the costs of training therapists will be established. The additional information collected after injurious falls will allow calculation of the medical, medical ancillary, diagnostic and hospitalization costs associated with these falls in the 12 months follow-up period. An incremental cost effectiveness ratio (ICER) will be calculated for the primary outcome as the difference in total cost per fall prevented between the IR and LS groups. For the secondary outcomes the ICER will be calculated for cost per injurious fall prevented and cost per quality adjusted life year saved.

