**Methods/design:**

180 community living people with PD will be randomly allocated to receive either a home-based integrated rehabilitation program (progressive resistance strength training, movement strategy training and falls education) or a home-based life skills program (control intervention). Both programs comprise one hour of treatment and one hour of structured homework per week over six weeks of home therapy. Blinded assessments occurring before therapy commences, the week after completion of therapy and 12 months following intervention will establish both the immediate and long-term benefits of home-based rehabilitation. The number of falls, number of repeat falls, falls rate and time to first fall will be the primary measures used to quantify outcome. The economic costs associated with injurious falls, and the costs of running the integrated rehabilitation program from a health system perspective will be established. The effects of intervention on motor and global disability and on quality of life will also be examined.

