## Methods/design

### Design

This study will be a prospective controlled trial with random allocation stratified by recruitment source to control for possible bias. Intention to treat analysis will be used and assessors blinded to group allocation. A concurrent economic analysis will evaluate the costs of falls and their management, as well as the costs of implementing the therapy intervention.

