### Interventions

The IR program and LS sessions will be delivered in participants’ homes by therapists trained in the appropriate intervention at a standardized training session conducted by the study team. Both IR and LS programs will run for six weeks. Interventions will comprise one 60 minutes session per week delivered by a therapist, plus a 60 minutes “homework” session performed by the participant following pre-printed but individualized worksheets. Physiotherapists will deliver the IR intervention and allied health professionals including occupational therapists and speech pathologists will run the LS sessions. Both the IR program and the LS sessions will occur in addition to participants’ usual healthcare.

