#### Integrated rehabilitation program

The IR participants will undertake a structured but individually tailored program of (i) progressive resistance strength training (PRST), (ii) movement strategy training (MST) and (iii) falls prevention education. This protocol integrates elements from interventions previously detailed by Morris et al. [27]. Written advice to therapists will assist them to schedule the time allocated between the various activities. Strength training exercises will be prioritized over other activities if a participant is unable to complete all three components within the allotted time for each session (60 minutes). The “homework” program will repeat activities from the therapist’s session for that week, modified to participant need and any safety issues. Pre-printed forms will be used to report the activities undertaken by each individual at each session and the amount of perceived effort used. Participants will record homework performance on similar forms. These data will enable later evaluation of adherence to and compliance with the interventions. Participants will be asked at each session whether they experienced any negative side effects of treatment such as muscle soreness or joint stiffness from the previous session, whether it required any health service attendance and the results recorded.

Participants will be given an intervention pack containing a booklet with the exercises pictured and described, a modified Rate of Perceived Exertion scale (mRPE) [56], an exercise log book (used to monitor compliance with the homework program), a sheet of frequently asked questions about strength training and a booklet on falls prevention [57]. They will also receive a standard help sheet from Parkinson’s Victoria listing resources for participant or caregiver support.

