### Life skills training

The control group’s LS sessions will be of equivalent duration to the IR program, with the same therapist-participant contact time and a weekly self-directed but structured “homework” session. The program will consist of a series of guided education and discussion sessions based on topics of interest. These will be selected by each participant from a pre-defined syllabus to optimize retention and interest. Topics include information on: relaxation; energy conservation; fatigue management; voice and communication; swallowing and diet; travel advice; and memory skills. No session content will relate to physical activity, exercise, walking, or falls risk education. Participants in the LS group will also be given a general intervention pack containing the standard help sheet from Parkinson Victoria, Australia. Ethics required us to provide a generic falls information sheet also.

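### Read plainly, the ICER subtracts the delivery cost of the contact-matched control sessions, which would understate the cost per fall prevented from the health-system perspective

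*Protocol article*

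**What the plan says.** The last paragraph of the Background (protocol article) sets the perspective of the economic evaluation as that of the health care system. The Economic evaluation section opens with its purpose: "To enable calculation of the costs of the intervention relative to the number of falls prevented", for which "the direct costs of implementing the therapy programs including the costs of training therapists will be established". It adds the care costs that follow injurious falls. It then defines the ratio for the primary outcome "as the difference in total cost per fall prevented between the IR and LS groups", and names two further ratios, per injurious fall prevented and per QALY. It does not itemise what total cost contains.

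Two other places describe the programme cost more narrowly. The Abstract (Methods/design) says "the costs of running the integrated rehabilitation program from a health system perspective will be established". The Design section says the economic analysis will cover the costs of falls "as well as the costs of implementing the therapy intervention".

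On the comparator, the Life skills training section says LS runs "with the same therapist-participant contact time" as IR. The Interventions section gives each arm one 60-minute therapist session a week for six weeks at home, delivered by physiotherapists (IR) or other allied health professionals (LS). It also says: "Both the IR program and the LS sessions will occur in addition to" usual care.

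The Integrated rehabilitation program section has therapists ask at each session about side effects of the previous one and "whether it required any health service attendance and the results recorded". These attendances do not appear among the costs named under Economic evaluation.

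**The concern.** A health system deciding whether to fund IR compares it with what it pays for now, which is usual care. LS is a trial control, there to equalise attention and contact. If its delivery and training are counted in the LS total, the between-arm difference sets six paid therapist hours against six paid therapist hours. Most of what it would cost to adopt IR then drops out of the numerator, while the falls prevented in the denominator stay the same. The ratio would describe replacing LS with IR, which is not the funding decision that the stated perspective implies. The ratios per injurious fall and per QALY use the same cost difference.

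The sections also support different numerators. The Abstract and Design point to the cost of IR alone; the Economic evaluation section, with its plural programs and its between-arm total, points to both. Two analysts following the article could report very different figures.

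**Working it through.** The article gives no ICER, unit cost or control fall rate, so there is no figure to reproduce. The check is algebra plus an illustration.

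**Inputs from the protocol article**
- Therapist contact: 6 weeks × one 60-minute visit = 6 visits per participant in each arm (Interventions; Life skills training).
- Planned effect: 25% reduction in falls frequency (Power calculation and sample size).

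**Assumptions, not in the article**
- Cost per visit c: 80 to 160 currency units.
- LS hourly cost: 90% to 100% of IR.
- Additional cost specific to IR: 0 to 150 per participant.
- Control rate m: 1 to 3 falls per person-year, with a one-year horizon.
- Fall-related care costs set equal between arms for the illustration.

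**Formulas.** Let P be programme cost, H fall-related care cost (both per participant), and F = 0.25 × m the falls prevented per participant.
- LS cost netted: [(P_IR + H_IR) − (P_LS + H_LS)] / F
- LS delivery and training excluded: [P_IR + H_IR − H_LS] / F
- Gap: P_LS / F

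The fall-care difference H_IR − H_LS appears in both versions and cancels from the gap, so savings in fall care do not change it.

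**Gap in visit costs**, counting the visits only and taking c equal in both arms: 6c / (0.25 × m).
- m = 1: 6c / 0.25 = 24c per fall prevented.
- m = 3: 6c / 0.75 = 8c per fall prevented.

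Any LS training cost would add to this.

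**Share of IR programme cost removed by netting**, P_LS / P_IR:
- Lowest in the assumed range (c = 80, LS at 90%, additional IR cost 150): (6 × 80 × 0.9) / (6 × 80 + 150) = 432 / 630 = 69%.
- Highest (equal hourly cost, no additional IR cost): 100%.

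**One worked case** (c = 120, equal hourly cost, additional IR cost 50): P_IR = 720 + 50 = 770 and P_LS = 720.

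| Control falls per year | Falls prevented (F) | LS netted | LS excluded |
|---|---|---|---|
| 1 | 0.25 | 50 / 0.25 = 200 | 770 / 0.25 = 3080 |
| 3 | 0.75 | 50 / 0.75 = 67 | 770 / 0.75 = 1027 |

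In this case, IR shows as cost-saving once fall-care savings exceed 50 per participant with netting, and only once they exceed 770 without it.

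**The case against.** **Netting is inferred.** Total cost is not itemised, and a between-arm difference is needed anyway for fall-related care. The purpose clause of the Economic evaluation section, the Design section and the Abstract all speak of the intervention or of IR. This stands in part: a reader might infer that the article expressly commits to subtracting LS delivery, and it does not. But the Abstract and Interventions use the word programs for both arms, the section defining the ratio uses the plural, and nothing excludes LS cost. Netting is the plain reading. Nor do the Abstract and Design flatly contradict it, since collecting both programmes' costs includes collecting IR's; they leave the numerator unsettled.

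**The size is not in the article.** This stands. A reader might conclude that IR would look almost free, or put a currency figure on the understatement. Both depend on unit costs and a control fall rate that the article does not give. Only the direction and the formula follow from the text.

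**Netting alone would not make IR cost-saving.** This also stands. With programme costs close to cancelling, IR appears cost-saving only if its fall-related costs are lower or its delivery is cheaper than LS. Netting lowers that threshold but does not by itself produce the result.

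**IR versus LS is the randomised comparison, and LS may do some good.** Its topics include fatigue management, energy conservation, and swallowing and diet, and LS participants also receive a generic falls information sheet. Dropping LS cost while keeping any LS benefit would bias the ratio against IR, most plausibly for QALYs. This stands, and is why both versions should be reported. It does not make the netted ratio an answer to the health-system question.

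**Side-effect attendances may simply be left to a fuller document.** That is fair: the named costs need not be exhaustive, and nothing shows that the amounts are material. Since the data are already collected, naming them is a minor addition, not a separate fault.

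**Conclusion.** The point holds as a conditional one. Followed on its plain reading, the stated formula understates the cost per fall prevented, from the health-system perspective, by LS programme cost divided by falls prevented. This assumes that IR prevents falls and that the system would not otherwise pay for LS. If the sponsor intended LS delivery and training to stay out of the LS total, there is no understatement from this source, and the fault is only that the sections do not say so.

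Under equal visit costs and the planned effect, the visits alone account for 8 to 24 visit costs per fall prevented over control rates of three to one falls per year. Across the wider assumed ranges, netting removes 69% to 100% of IR programme cost. These sizes are illustrations. The ratio of IR to LS is arithmetically valid for that comparison; what it lacks is relevance to the funding decision. The clinical falls comparison is unaffected.

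**What to change.** In the Economic evaluation section:
- **Cost per fall and per injurious fall prevented.** Define incremental cost as IR delivery and training, plus the IR minus LS difference in fall-related costs, with LS delivery and training excluded. Report the version that nets LS cost alongside it.
- **Cost per QALY.** Report both versions, and state that excluding LS cost assumes LS brings no quality-of-life benefit over usual care.
- **Side effects.** Add the health-service attendances for IR side effects, which the therapists already record, to the IR cost.
- **Consistency.** Make the Abstract, Design and Economic evaluation sections describe the same programme cost.

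The cost is some rewording and one extra run. No new data collection is needed. The price is a less favourable headline ratio for IR.

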### Statistical analysis

#### Primary

Falls, as the primary variable of interest, will be examined in four ways consistent with the recommendations of the ProFaNe group [60]:

i. number of fallers

ii. number of multiple fallers (two or more falls)

iii. falls rate and time to first fall

iv. relative risk (RR) will be calculated to compare number of fallers and number of multiple fallers between the two groups.

The number of falls and the falls rate per person per year in the two groups will then be compared using negative binomial regression models, an approach that takes into account all falls and adjusts for varying duration of follow up. Injurious falls, as defined above, will be analyzed in the same way.

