## Background

Most people with idiopathic Parkinson’s disease (PD) live at home or in the community. A major aim of physical therapy is to enable them to remain at home safely for as long as possible [1-3]. Even though it is estimated that more than 7 million people worldwide have PD [4], there have been few investigations of the most effective home-based exercise and rehabilitation programs for those with this debilitating condition. Falls occur often in people with idiopathic PD as the disease progresses [5,6], with fall rates of over 60% per annum reported [7,8]. More than half of these individuals fall more than once every year [8-10]. It appears likely that the cognitive difficulties frequently associated with PD aggravate the risk of falling, particularly by impairing attention [11].

Potential injury is not the only adverse consequence of a fall. Falling may lead to a fear of falling [12,13], which can in turn result in further falls [14,15]. In people with PD, fear of falling has been associated with an increased risk of frequent falls [16]. Falls often lead a person to reduce their activity levels [14,17,18], community ambulation [19] and their participation in outdoor activities [20], leading to loss of fitness and independence.

Falls not only compromise quality of life [21], but can sometimes impact negatively on caregiver quality of life, with reported issues including depression, sustained productivity losses, fear for their spouse, and injuries sustained in trying to prevent their spouse’s fall [22,23]. The costs from health care service utilization following falls are also substantial [24]. A recent study [25] found annual direct costs of medical care in the USA to be $US23,101 per person in people with PD and only $US11,247 in matched controls, noting that falls were substantial contributors to the difference.

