### Power calculation and sample size

The primary dependent variable of falls frequency over 12 months was used to determine sample size. Based on previous studies [8,52] and setting power at 80%, alpha at 5% and with a drop-out rate of 20%, a sample size of 90 is required in each group to detect a clinically significant difference of 25% reduction in falls frequency in the intervention group. This sample size will also be sufficient to identify between-group differences in the secondary outcomes of the Movement Disorders Society – Unified Parkinson’s Disease Rating Scale (MDS-UPDRS) [53] and Parkinson’s Disease Questionnaire-39 items (PDQ-39) [54,55].

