### Randomization and blinding

One hundred and eighty people with Parkinson’s will be randomly allocated to either the intervention group (integrated rehabilitation program (IR)) or the control group who will participate in life skills information sessions (LS). Randomization will be stratified according to each referral source in permuted blocks of 6, 8 and 10 by an independent private trials coordination organization. Those involved in recruitment and assessment will be blind to group allocation.

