### Assessments

All assessments will be performed in the participant’s home by a trained physiotherapist blind to group allocation. Participants will be reminded not to disclose their treatment or group allocation to the assessor. Assessments will occur in the week prior to therapy commencing (T1), in the week after six weeks’ therapy (T2) and 12 months after therapy completion (T3). Difference between T1 – T2 assessments will allow evaluation of the immediate effect of therapy, while T2 to T3 difference will determine whether the IR program has a longer term effect. Each assessment will include the MDS-UPDRS [53], PDQ39 [54,55] and the EuroQol EQ-5D^TM^[58]. Medications and their dosage will be recorded on each test occasion.

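### The primary negative binomial comparison names follow-up time as its only adjustment; recruitment source and baseline MDS-UPDRS should be pre-specified in the model for a modest, conditional gain in precision

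*Protocol article*

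**What the plan says.** Under Statistical analysis, Primary, falls are first described as fallers, multiple fallers, falls rate and time to first fall. The number of falls and the yearly rate per person "in the two groups will then be compared using negative binomial regression models". The article justifies this choice on two grounds: the method uses every fall, and it adjusts for unequal follow-up. No other adjustment is named, and none is ruled out.

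Three other places bear on the model:
- **Randomization and blinding:** "Randomization will be stratified according to each referral source in permuted blocks of 6, 8 and 10". The Design section gives control of possible bias as the reason for stratifying by recruitment source.
- **Assessments:** T1 falls in the week before therapy starts. "Each assessment will include the MDS-UPDRS", together with the PDQ-39, the EQ-5D and a record of medication.
- **Background:** "Falls occur often in people with idiopathic PD as the disease progresses".

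**The concern.** The design uses recruitment source to protect the comparison, but the stated analysis does not mention it again. Blocking within source balances source across the arms. If source predicts falls, a model without it still counts the between-source variation as error, so its standard error is too large for the design that was used.

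Baseline severity is a slightly different case. It is not balanced by design, so a model without it has a valid standard error, but a larger one than the data allow. By the article's own account severity is related to falling, and a pre-therapy measure of it will be on file for the participants.

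What is at stake is precision. Fall counts are usually overdispersed, and the between-person part of the variance does not shrink as people fall more often. Covariates that explain some of that part narrow the confidence interval without adding participants.

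**Working it through.** **1. The plan's own figure.** The article requires 90 per group at 80% power, alpha 5% and 20% drop-out, for a "clinically significant difference of 25% reduction in falls frequency in the intervention group". The drop-out step checks: 72 / 0.8 = 90, so 72 evaluable per arm. The 72 itself cannot be reproduced, because no control fall rate, dispersion or standard deviation is given.

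**2. Inputs.**
- Rate ratio 0.75: the 25% reduction, read as a reduction in rate (Power calculation and sample size).
- 72 evaluable per arm: step 1.
- 60% fallers in a year among controls: the Background reports over 60%.
- Dispersion k of 1 to 2: assumed.
- Share r of dispersion explained by covariates, 10% to 30%: assumed.
- One year of follow-up and two-sided alpha: assumed. The article monitors falls for 6 weeks plus 12 months and does not state sidedness.

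**3. Mean implied by 60% fallers.** For a negative binomial count, P(0) = (1 + kμ)^(−1/k) = 0.4.
- k = 1: 1 + μ = 2.5, so μ = 1.5.
- k = 2: 1 + 2μ = 6.25, so μ = 2.625.

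**4. Variance of the log rate ratio, times n per arm.** V = 1/μ + 1/(0.75μ) + 2k.
- k = 1: 0.667 + 0.889 + 2 = 3.556. Dispersion is 2/3.556 = 56% of it.
- k = 2: 0.381 + 0.508 + 4 = 4.889. Dispersion is 4/4.889 = 82% of it.

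**5. Effect of adjustment.** Replace 2k by 2k(1 − r). The cut in V is 2kr/V.

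| k | r | Cut in variance | Equivalent extra participants |
|---|---|---|---|
| 1 | 10% | 0.2/3.556 = 5.6% | 3.556/3.356 = 1.06, about 6% |
| 1 | 30% | 0.6/3.556 = 16.9% | 3.556/2.956 = 1.20, about 20% |
| 2 | 10% | 0.4/4.889 = 8.2% | 4.889/4.489 = 1.09, about 9% |
| 2 | 30% | 1.2/4.889 = 24.5% | 4.889/3.689 = 1.33, about 33% |

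The top of the range pairs the highest assumed k with the highest assumed share.

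**6. A lower dispersion.** The Background also says that more than half of these individuals fall more than once a year. If that means more than half of fallers, then at exactly 60% fallers a negative binomial needs k of about 0.45 or more. At k = 0.45, μ = 1.134 and V = 0.882 + 1.176 + 0.9 = 2.958. The cut is then 0.09/2.958 = 3% to 0.27/2.958 = 9%. This floor is fragile: it drops to about 0.24 at 65% fallers and about 0.05 at 70%.

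**7. What it does to power.** Power ≈ Φ(0.2877/√(V/72) − 1.96), where 0.2877 = −ln 0.75.
- k = 1: 25% unadjusted, 27% at r = 10%, 29% at r = 30%.
- k = 2: 20% unadjusted, 21% at r = 10%, 25% at r = 30%.

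Other assumed control rates give different levels. With r = 20%:
- 3 falls a year, k = 1: from 31% to 35%.
- 5 falls a year, k = 0.5: from 52% to 58%.
- 10 falls a year, k = 1: from 37% to 44%.

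Without adjustment, 72 per arm reaches 80% only if k is at most about 0.15 at 5 falls a year, 0.26 at 10, or 0.32 at 20. So the power level depends on the assumed rate and k. In each scenario shown, the gain from adjustment is a few points.

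**The case against.** The strongest objection is that this is silence, not a decision. The source is a condensed journal article, covariate lists commonly sit in a full protocol or analysis plan, and the remark about follow-up explains why the method was chosen. That stands against one tempting reading: a reader might infer that the trial has chosen a bare two-group model and deliberately set aside its stratification factor. The article does not say so. What survives is narrower. The text names the model and one adjustment, so an analyst following it would fit treatment and an offset, and a specific better model is available from data already planned.

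Further objections also hold:
- **No bias.** A reader might infer that leaving out the stratum distorts the treatment effect. It does not. Allocation is randomized, the rate ratio under a log link is essentially unchanged by adjustment, and the blocking already limits imbalance in source. At worst the test is somewhat conservative.
- **No documented difference by source.** The article does not say that people recruited through neurologists and through the support group fall at different rates, and the same eligibility criteria apply to both. If the rates are alike, adding source gains almost nothing.
- **No strength of association for severity.** The Background links falls to disease progression but gives no figure relating MDS-UPDRS to fall counts.
- **Other predictors are not listed.** Hoehn and Yahr stage appears only as an eligibility limit, and falls before enrolment are not among the T1 assessments.

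**Conclusion.** The point holds as a recommendation to improve precision, not as a finding of an invalid analysis. The stated model names follow-up duration alone, while the stratification factor and a pre-therapy severity measure will both be available. Under the assumptions above, adding them cuts the variance of the log rate ratio by about 6% to 25%, or about 3% to 9% if k is nearer 0.45. The dispersion and the share explained are assumed throughout; only the 60% fallers, the 25% reduction and the 72 evaluable come from the article or follow from it.

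A reader might also infer that the trial is shown to be badly underpowered and that adjustment is the remedy. The document supports neither. Its power cannot be derived without a control rate and a dispersion. Where power is low under assumed values, adjustment adds a few points and does not by itself bring it back to 80%.

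**What to change.** State before unblinding that the primary negative binomial model contains treatment, a log person-time offset, recruitment source as used in the randomization, and baseline (T1) MDS-UPDRS total. Report the model without source and MDS-UPDRS as a sensitivity analysis. If a separate analysis plan already says this, confirming it is enough.

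Two details should be fixed at the same time: how MDS-UPDRS enters (for example as a linear term), and how sparse strata are pooled, since the article does not say how many referral sources count as strata. Hoehn and Yahr stage and a prior-falls question should not be part of this change, because neither is listed as a baseline assessment.

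The cost is a sentence or two of analysis wording. No new data, visits or participants are needed, and fixing the covariates in advance removes the scope for choosing them after the results are seen.
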